### Power analysis

The sample calculation and power analysis is based on α = 0.05 at a power of 0.80, using the pre/post differences of the mentioned FPS. We expect at least an effect size of *d* = 0.5. Further, if we used a RCT study design for analysis of variances, the minimum sample size would be *n* = 63 per treatment. In contrast, we applied a CRCT design with the daycare centers as given clusters. (Note: each daycare center represents one cluster.) We used a formula introduced by Eldridge *et al*. [45], providing a conservative estimate of sample size requirements for trials using cluster-level analyses weighted by cluster size.

$$n*=\left\{1+\left[\left(1+\mathrm{CV}2\right)\times m–1\right]\times \mathrm{ICC}\right\}\times n$$

The formula for the corrected sample size *n** consists of the coefficient of variation *CV* for trials with unequal cluster sizes (that means with unequal sizes of daycare centers) and the intra class correlation coefficient *ICC* within the clusters and the mean cluster size *m*. Using again the findings of the Frankfurt Prevention Study, the estimated coefficient of variation is *CV* = 0.467 and the estimated intra class correlation coefficient (based on the pre/post differences including the *CV*) *ICC* = 0.0465. We expect a mean cluster size *m* = 20 or at least *m* = 17 children. The corrected sample size for the first scenario would be *n** = 131.44 (if *m* = 20) divided by 20 = 6.57; in the second scenario *n**=120.73 (if *m* = 17) divided by 17 *n** = 7.10. For both scenarios, seven clusters, respectively seven daycare centers per treatment, should be selected.

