### Planned analyses for the primary outcome

#### Primary outcome: MCAST attachment representation

Data will be analyzed with respect to the intention of treatment. We will describe all baseline characteristics at the individual as well as at the cluster level. Moreover, we will assess the characteristics of any cluster and if the children drop out. Relevant characteristics will be added if applicable as covariates to the models. Children’s attachment representations are measured on MCAST’s overall attachment classification (secure vs insecure-ambivalent vs insecure-avoidant vs insecure-disorganized attachment representation) and on MCAST’s disorganization and narrative coherence scores. As the main analysis involves changes in MCAST disorganization and narrative coherence scores from the baseline and the endpoint in the intervention versus the control group, an analysis of covariance is applied with repeated measures and linear regression with autocorrelated data (compound symmetric covariance structure models). Changes in the overall attachment classifications are calculated by tests for frequency distributions and procedures of survival analysis (Cox, regression, log-rank tests). All procedures take the CRCT design into account. Therefore, variances of the sample mean will be corrected using the factor *n**/*n* (as described above).

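### The primary analysis corrects for clustering with the planning design effect, so, read literally, its standard errors rest on an ICC from an earlier study and not on EVA's own between-center variation

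*Protocol article*

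**What the plan says.** Under the primary-outcome heading of the planned analyses, the main analysis is described this way: "As the main analysis involves changes in MCAST disorganization and narrative coherence scores from the baseline and the endpoint", compared between arms. The methods named are analysis of covariance with repeated measures and "linear regression with autocorrelated data (compound symmetric covariance structure models". Changes in the overall attachment classification go to frequency tests and survival procedures. The section then says that all procedures respect the cluster design, and gives the means: "Therefore, variances of the sample mean will be corrected using the factor" `n*/n`, with a pointer back to the earlier description.

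That description is in the Power analysis section. It gives `n*` as a formula in the coefficient of variation of cluster size, the mean cluster size m and the ICC. It then puts in values from elsewhere: "Using again the findings of the Frankfurt Prevention Study, the estimated coefficient of variation is" 0.467, and the ICC, based on pre/post differences, is 0.0465. It evaluates the formula for m = 20 and m = 17.

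**The concern.** A design effect with an assumed ICC is a tool for sizing a trial. Used as the analysis correction, it makes the standard error of the arm comparison independent of how much the 14 daycare centers actually differ. The test then has its nominal level only if the MCAST ICC is close to the assumed value.

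The article gives little reason to expect that. The results it reports for the earlier study (Background) are aggressiveness, anxiety and hyperactivity, whereas MCAST is a story task administered by trained psychologists (Assessments). The earlier study covered low, middle and high socioeconomic status, whereas EVA targets deprived areas. The abstract says attachment data are being collected in such neighborhoods for the first time.

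The named compound symmetric structure does not fill the gap. The text ties it to repeated, autocorrelated measurements and names no center-level term. At stake is the width of every primary confidence interval and the level of every primary test.

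**Working it through.** **Inputs, all from the Power analysis section.** "The sample calculation and power analysis is based on α = 0.05 at a power of 0.80"; "We expect at least an effect size of *d* = 0.5"; "the minimum sample size would be *n* = 63 per treatment"; CV = 0.467; ICC = 0.0465; m = 20 or 17. Sidedness is not stated. A two-sided test reproduces 63 per arm, and a one-sided test would give 50. The Randomization section gives 14 centers, and the power section 7 per arm.

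**Reproducing the plan's figures.** Design effect: DE = 1 + [(1 + CV²) × m − 1] × ICC, with 1 + 0.467² = 1.2181.

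- m = 20: 1 + 23.362 × 0.0465 = 2.0863; × 63 = 131.44.
- m = 17: 1 + 19.708 × 0.0465 = 1.9164; × 63 = 120.73.

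Both match. The factor `n*/n` is therefore 131.44/63 = 2.086 or 120.73/63 = 1.916. The analysis section does not say which applies.

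**Effect of holding the factor fixed.** If the true MCAST ICC gives design effect DE_true, the actual two-sided type I error is 2 × [1 − Φ(1.96 × √(DE_planned / DE_true))]. The ICC values below are assumed.

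| True ICC | DE_true, m = 20 | Type I error, m = 20 | DE_true, m = 17 | Type I error, m = 17 |
|---|---|---|---|---|
| 0 | 1.000 | 0.5% | 1.000 | 0.7% |
| 0.02 | 1.467 | 1.9% | 1.394 | 2.2% |
| 0.0465 | 2.086 | 5.0% | 1.916 | 5.0% |
| 0.06 | 2.402 | 6.8% | 2.182 | 6.6% |
| 0.08 | 2.869 | 9.5% | 2.577 | 9.1% |
| 0.10 | 3.336 | 12.1% | 2.971 | 11.5% |

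Worked case, ICC 0.10 and m = 20: the standard error is too small by a factor of √(3.336/2.086) = 1.265. The effective critical value is 1.96/1.265 = 1.55, so type I error is 12.1% and a nominal 95% interval covers about 88%.

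**Simulation check.** With 7 + 7 centers, gamma-distributed sizes (mean 20, CV 0.467) and 20,000 runs per ICC, the fixed factor gave 1.9% at ICC 0.02, 4.9% at 0.0465, 8.8% at 0.08 and 11.7% at 0.10. Using the realized m and CV but keeping ICC = 0.0465 still gave 11.8% at 0.10, so the ICC is what matters. A t test on center means (12 df) stayed between 4.7% and 5.2% at every ICC tried.

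**How firm the borrowed ICC is.** The Background says the earlier study also had 14 centers. If the true ICC were 0.0465, an estimate from 14 centers of 20 children would have a central 95% range of about −0.01 to 0.13.

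**The case against.** The strongest counter-argument is that the analysis section names a factor and does not restate 0.0465. The power section gives a formula and evaluates it for two scenarios, so at least m must be settled when the factor is applied. One could therefore read the plan as applying the formula to EVA's own ICC, CV and m, and a condensed article may leave that to a fuller document. That reading is open, but the text does not state it, and the back-reference points to the planning values. So the point is limited to the literal reading and to the absence of any statement that the ICC is re-estimated.

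Three stronger conclusions are tempting and are not supported:

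- A reader might infer that the primary results are invalid unless MCAST has exactly this ICC. Below 0.0465 the test is only conservative: type I error stays under 5% and power is lost.
- A reader might take 11–12% as the trial's actual error rate. It requires an ICC about twice the planning value, and the article gives no MCAST ICC in either direction.
- A reader might add that compound symmetry wrongly forces equal correlation over the unequal 24- and 12-month gaps. The stated main contrast is baseline to endpoint. With two time points there is only one within-child correlation, so nothing is restricted.

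**Conclusion.** The concern holds as a badly fixed analysis rule. As written, clustering in every primary analysis is handled by a constant from the sample-size calculation, and EVA's own between-center variation does not enter the standard errors. The direction of the error is unknown. Over an assumed ICC range of 0.02 to 0.10, the nominal 5% test has an actual level of about 2% to 12%, and it equals 5% only near 0.0465. This rests on the literal reading of the back-reference, 7 centers per arm, m of 17 to 20 and CV of 0.467. It shows sensitivity to an unknown quantity and does not demonstrate that the trial's error rate is inflated.

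The same factor is also meant for the frequency tests and survival procedures, and the article gives no reason why an ICC from pre/post differences in another study should suit them.

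**What to change.** Use `n*/n` for planning only, and replace the correction sentence with rules that estimate center-level variance from EVA data.

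- **MCAST disorganization and narrative coherence scores.** Model the t2 score on arm and baseline score, with a random intercept for daycare center and small-sample degrees of freedom. A t test (12 df) or permutation test on baseline-adjusted center means would also do.
- **If baseline is kept as a repeated outcome.** Include a center-by-time random effect. A constant center intercept cancels from the arm-by-time contrast and would leave the clustering of change unmodeled. At an ICC of 0.0465 for change, ignoring it gives 2 × [1 − Φ(1.96/√1.916)] = 15.7% (m = 17) or 2 × [1 − Φ(1.96/√2.086)] = 17.5% (m = 20).
- **Classification and survival analyses.** Replace the fixed factor here too, with a cluster-level or permutation analysis or a center random effect with small-sample correction. Otherwise, removing the sentence would leave these analyses with no stated allowance for clustering.
- **Reporting.** Give the ICC estimated in EVA for each primary measure.

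If re-estimating the ICC within the formula was the intention, the plan should say so, and it would still need small-sample degrees of freedom with 14 centers.

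The cost is a change of wording and standard software. Intervals will be somewhat wider than with an ICC treated as known. At ICC 0.0465 and 7 centers per arm, power is 75.8% (m = 20) or 72.5% (m = 17) with a 12-df t reference, against 82.5% or 79.6% by the normal approximation.

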### Ethical issues

The Ethic Review Commission of the Federal Chamber of Child and Adolescent Psychotherapists of the State of Hessen, Germany, have approved the final study protocol and the final version of the written informed consent form. Written consent was obtained from each participating family.

### Status of the study

Ongoing recruitment.

## Discussion

The EVA study is carried out in the Center for Research on Individual Development and Adaptive Education of Children at Risk (IDeA) with financial support from the State of Hessen, Germany. One major aim of the IDeA Center is to improve the social integration and positive development of children at risk. Previous studies showed evidence of accumulation of psychosocial problems in socioeconomically deprived neighborhoods [5-8,47] and found that parenting characteristics moderate the association between SES and children’s cognitive and academic achievements [4]. Therefore, the EVA study investigates children at risk in socioeconomically deprived neighborhoods where their families face multiple challenges. Moreover, findings of attachment research influenced the EVA study design. Hence, attachment representations as crucial moderators for child development [43] highlight the importance of a ‘good enough’ early child–parent relationship experience. A secure attachment relationship between infant and caregiver is associated with optimal infant development and positive social development, including higher levels of social competence, more advanced emotional understanding and higher cognitive and language skills [48,49]. In contrast, children with an insecure-disorganized attachment representation show the highest risk later, demonstrating behavior problems that include clinical levels of externalizing and/or aggressive symptoms, hostility in the classroom as well as poor academic achievement [50-52]. This knowledge motivated us to implement an instrument in the EVA study design to classify children’s attachment representations using the MCAST. We expect to find a high- risk population regarding children’s attachment representations and to detect a high percentage of insecurely attached children. Several program modules of Early Steps (such as psychotherapy for children and their parents within the daycare center and the individual mentoring by student teachers during the transition from kindergarten to primary school) particularly address children at risk, respectively children with insecure-disorganized attachment representations. Especially for these children, we expect an improvement of their attachment representation after the individual treatment in the Early Steps group.

Since both interventions Faustlos and Early Steps have been previously evaluated and the aim of this trial is further to compare their respective effectiveness in improving behavioral and attachment related outcomes among high-risk children, we included a process evaluation in the design. The aim of this evaluation is to document the context in which the interventions were implanted and how the potentially relevant mechanisms may or may not work. We assumed that the institutional settings (for example, management style, participation possibilities for parents, quality of team work among teachers, fluctuation of teachers, frequency of families with multiple problems, open, half-open, or closed groups of children) could be determined as moderating factors for effectiveness. Therefore, regular meetings at least every 6 months were established for the directors of all participating daycare centers. During these meetings, teachers are invited to share their experiences and to discuss the ongoing process of implementing the prevention program. Regarding the Early Steps program, most questions involve considerations about the cooperation and fit between psychotherapist and teachers, psychotherapist and parents, psychotherapist and children, as well as between the supervisor and the teacher’s team. Faustlos meetings would probably concentrate on the match between the teacher administering Faustlos and the children, as well as on further adaptations of the program into the daily regime of the daycare center. In order to attain a description over time of these context and setting factors, minutes are made of the meetings. Additionally, each daycare center has at least one ‘mentor’ from the research team who will continually accompany the daycare center and their teachers during the whole intervention period and thus serve as a contact person for questions and complaints. The mentors take notes on their contacts with the personnel. The third information source of this process of implementing the program involves regular meetings between the psychotherapists and supervisors for the teams. The appraisals of these three sources are then sorted into variables, as described in the second hypothesis, in order to study their influence on the effectiveness of the programs.

One main point of interest of the IDeA Centers with high practice relevancy focuses on the professionalization of the teachers. Within the framework of this research emphasis, the EVA study assesses the impact of the team supervision for the teachers that takes place every 2 weeks in the Early Steps intervention branch, hypothesizing a process of professionalization enabling improved mentalizing and reflective processes among its teachers. We apply an instrument, the Self-Reflective Functioning Scale [39,40], which originated in attachment theory research and forms the basis for the concept of mentalizing. Fonagy *et al*. [39] define mentalizing as the ability for implicitly and explicitly interpreting the actions of oneself and others as meaningful mental states (for example, desires, needs, feelings, beliefs, and reasons). Good mentalizing in relation to other’s thoughts and feelings is characterized by the acknowledgement of opaqueness, absence of paranoia, of contemplation and reflection, perspective taking, genuine interest, openness to discovery, forgiveness, and predictability. In contrast, poor mentalizing contains an anti-reflection perspective with hostility, active evasion and non-verbal reactions, failure of adequate elaboration with a lack of integration and explanation as well as inappropriate reactions such as illogical assumptions, gross conjectures about the interviewer and taking the meanings of words literally. In our review of the process evaluation, we study the ability and the quality of mentalizing and reflection in the teachers as a prerequisite for professional work in educating children. Experiences of the Frankfurt Prevention Study [26-28] show that this professionalization takes much time to build the necessary confidence and that perhaps it may not yet have lead to the wished effects during the 2-year period of the project. In order to study the differential long-term effects of both intervention programs, we propose further follow-up studies of children in intervals between 3 and 5 years that would reach beyond the above study design.

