The study ‘Evaluation of two prevention programs ‘Early Steps’ and ‘Faustlos’ in daycare centers with children at risk’ (EVA) compares the differential effects of two established prevention programs. Both prevention programs have been rigorously evaluated in the past [26-30]. The EVA study aims at reviewing whether the additional expenses for prevention program 1, Early Steps, is justified in the short and long term in comparison to prevention program 2, Faustlos. Taking into account one of the major findings of the large Head Start program [31], we formulated as one of our main hypotheses that, for children with a high developmental risk (for example, with a disorganized attachment pattern), the standardized, non-individualized Faustlos program will prove not to be sufficient for improving the social integration and the prevention of aggression of these children. We hypothesize that the more complex, individualized and costly Early Steps program will show positive effects on the social behavior of children at risk developmentally. Moreover, we expect the institutional setting/structure of the daycare centers to be a moderator variable. By this, we mean that the institutional setting of the daycare center (management style; participation possibilities for parents; quality of team work among teachers; fluctuation of teachers; frequency of families with multiple problems; open, half-open, or closed groups of children) influences the fit between daycare center and prevention program. For example, a daycare center with the following characteristics: a strict, top down management style, restricted/limited parent participation, high teacher fluctuation, but low frequency of families with multiple problems, might show a better fit to the Faustlos program and, therefore, might show better results in preventing aggression instead of the Early Steps program in a daycare center with the same characteristics.

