#### The ‘Early Steps’ intervention

The multi-perspective and multi-component prevention program [26] Early Steps is characterized by its approach that starts with a detailed understanding of an individual child and its family. Each child is unique, as is each family. This approach is especially helpful if the specific skills and resources of the individual child are taken as the starting point. Hence, a child’s behavior is not seen primarily as ‘dysfunctional behavior’, but rather as the expression of a hidden (unconscious), reasonable, emotional development. Thus, the specific and perhaps conspicuous behavior of a child needs first to be understood and should not be simply disregarded. The aims of the supportive measures of the study are to allow the child to achieve more positive experiences of itself and its attachment figures and to develop its talents in an optimal way. Early Steps is conducted in close cooperation with the Institute for Analytical Child and Adolescence Psychotherapy. All 13 psychoanalytic therapists and supervisors in the study have at least 15 years of clinical experience in treating children and families and supervising groups (except 1 therapist with 5 years of experience). Early Steps consists of different elements:

•Biweekly case supervision of the daycare center team.

•Weekly proposal of counseling and training for educators and parents in the daycare center by experienced psychoanalytic child and adolescent psychotherapists.

•In individual cases, the proposal of therapy for children and their parents within the facilities.

•Faustlos violence prevention program in the second year of the project at the earliest.

•If required, individual mentoring of children by student teachers in their transition from kindergarten to primary school.

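### Institutional-setting moderators for the second hypothesis come from records made during the intervention, one source apparently Early Steps only, so the arm-by-setting analysis is open to bias of unknown size and direction

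*Protocol article*

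**What the plan says.** The Background section of the protocol article names the institutional setting as an expected moderator. Its list covers management style, parents' scope to participate, "quality of team work among teachers; fluctuation of teachers; frequency of families with multiple problems", and the type of children's group. The Objectives section makes fit between program and institution the second of three hypotheses.

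The Discussion says how the setting variables are obtained. Three streams of information are collected while the programs run:

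- minutes of directors' meetings, held at least every six months in all centers;
- notes by research-team mentors, who stay with each center throughout the intervention;
- a last stream, described thus: "The third information source of this process of implementing the program involves regular meetings between the psychotherapists and supervisors for the teams".

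Then: "The appraisals of these three sources are then sorted into variables, as described in the second hypothesis", so that their influence on program effectiveness can be studied.

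Psychotherapists and team supervisors are described only as part of Early Steps, whose elements include "Biweekly case supervision of the daycare center team" and weekly counseling for educators and parents. For Faustlos, the article describes a certified educator who trains the teachers.

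**The concern.** An effect modifier should be fixed before the intervention and measured alike in both arms. Otherwise the analysis cannot separate a program that works differently in different settings from a program that changes, or changes the recording of, the setting.

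Three features of the plan raise that problem. One source seems to have no Faustlos counterpart. The shared source also differs: the Discussion expects Early Steps directors' meetings to dwell on cooperation with the psychotherapist and supervisor, and Faustlos meetings on the match between teacher and children and on fitting the lessons into the day. Finally, quality of team work, and possibly parent participation, are things that supervision and counseling could alter.

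At stake is whether an apparent fit between program and institution, or its absence, can be believed. The primary MCAST comparison does not use these variables.

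**Working it through.** **1. Is there a pre-intervention or common source?** The sections compare as follows.

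| Section | What it gives |
|---|---|
| Discussion | Three sources, all tied to implementation |
| The 'Early Steps' intervention; Discussion (team supervision) | Psychotherapists and supervisors placed in Early Steps |
| The 'Faustlos' intervention | Certified educator only |
| Design | Centers were assessed before randomization, but institutional setting is not named |
| Representativeness; Neighborhood community risk | Baseline data on child behavior, SES and welfare dependency |

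No section describes a baseline measure of institutional setting. That the last source is missing in Faustlos is an inference from these sections; nothing contradicts it.

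**2. The plan's own sample size.** Inputs from the Power analysis section: "The sample calculation and power analysis is based on α = 0.05 at a power of 0.80"; "We expect at least an effect size of *d* = 0.5"; "the estimated coefficient of variation is *CV* = 0.467"; ICC = 0.0465; m = 20 or 17. A two-sided test is assumed.

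- Individual randomization: n = 2(1.960 + 0.842)²/0.5² = 62.8, rounded up to 63. This matches "the minimum sample size would be *n* = 63 per treatment".
- Design effect DE = 1 + [(1 + CV²)m − 1] × ICC = 2.0863 (m = 20) or 1.9164 (m = 17).
- n* = 63 × DE = 131.44 or 120.73, that is 6.57 or 7.10 clusters. The plan's figures reproduce.

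**3. When does arm-dependent measurement bias the interaction?** Take the center-level model Y = 0.5T + cM + error, with T = 1 for Early Steps, M the true setting (SD 1) and no true interaction. The analysis regresses Y on T, the recorded setting W, and T × W. The SD of a center mean given M is √[0.0465 + (1 − 0.0465)/17] = 0.320. All values of c, reliability and feedback below are assumptions, because the documents give none. Type I error is from simulation with 7 + 7 centers, m = 17 and 8,000 runs.

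| Scenario | Large-sample interaction | Simulated mean | Type I error |
|---|---|---|---|
| Same accurate measure in both arms, c = 0.3 | 0 | 0.00 | 4.9% |
| Equal error in both arms (reliability 0.67), c = 0.3 | 0 | 0.00 | 4.8% |
| Uniform 1 SD shift in Early Steps, c = 0.3 | 0 | 0.00 | 4.9% |
| Reliability 0.75 vs 0.67 (three sources vs two), c = 0.3 | 0.3 × (0.75 − 0.667) = 0.025 | 0.03 | 5.4% |
| Reliability 0.9 vs 0.5, c = 0.3 | 0.3 × (0.9 − 0.5) = 0.12 | 0.12 | 8.9% |
| Early Steps notes partly reflect the center's outcome (g = 0.5), c = 0 | 0.5 × 0.320/(1 + 1/3 + 0.25) = 0.10 | 0.10 | 8.6% |
| Same, g = 1 | 0.320/(1 + 1/3 + 1) = 0.14 | 0.14 | 17.3% |

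In the last two rows, g is the weight of the standardized outcome error in the Early Steps record, and the reliabilities before feedback are 0.75 and 0.67. The large-sample column shows that more centers would not remove these biases.

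Under the uniform shift the interaction is safe, but the program effect at a fixed recorded setting becomes 0.5 − 0.3 × 1 = 0.2 instead of 0.5.

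**4. Power for an interaction, whatever the measurement.** Assume a two-level feature split 4/3 within each arm, giving 14 − 4 = 10 df.

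- SE = √[DE/m × (1/4 + 1/3 + 1/4 + 1/3)] = 0.349 (m = 20) or 0.363 (m = 17).
- By the noncentral t distribution, power for 0.5 SD is about 25% or 24%, and 80% power needs 1.08 or 1.13 SD.

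**The case against.** The case for leaving the plan alone has real substance.

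- **The damage may be small.** The scenario closest to one extra source in one arm moved type I error only to 5.4%. The larger distortions rest on assumed reliabilities or feedback. This stands: a reader might infer that the interaction is certainly biased or that the hypothesis is unanswerable, and the documents do not support either.
- **The obvious example fails.** It is tempting to say that Early Steps makes its centers less rigid and so manufactures a Faustlos advantage in rigid ones. If the change is uniform, it does not. The change must be unequal across centers.
- **Coding is not described.** A reader might infer that people who know the allocation sort the notes after the outcomes are in. The article says neither who codes nor when, and it may leave that to a fuller document.
- **Several features are largely structural.** No Early Steps element is described as aimed at management style, group type or the frequency of multi-problem families. The Discussion also doubts whether professionalization will show its effects within two years.
- **Low power is a separate matter.** The figures in step 4 would be the same with perfect baseline moderators, so they do not measure this defect.
- **The framing is cautious.** The material sits within a process evaluation, and the hypothesis is worded tentatively.

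The source of the variables still stands as a weakness. It is a choice the article states, not a detail it omits, and process notes that serve well to describe context are a poor basis for effect modifiers.

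**Conclusion.** The concern holds as a risk, not as a demonstrated bias. The moderators are to be built from records made during implementation, with one source apparently confined to Early Steps and a shared source whose content is expected to differ by arm. The arm-by-setting analysis is therefore open to bias if reliability differs by arm, if notes reflect how the program is going, or if the program changes centers unequally. A uniform shift would distort only the program effect at a given setting.

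Size and direction cannot be derived from the documents. The 5.4% to 17.3% range of type I error illustrates assumed scenarios and is not an estimate for this trial. The conclusion rests on the inference that Faustlos centers have no psychotherapist and supervisor meetings, and on the absence of any described baseline measure of setting. It touches the second hypothesis only. The change is worth making but does not threaten the trial's main result.

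**What to change.** Amend the process-evaluation text in the Discussion, and carry the change into the analysis plan:

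1. Exclude the psychotherapist and supervisor meetings from moderator coding. Keep them, and later notes from any source, for describing process.
2. Code institutional setting once per center, on one common form, from sources available in both arms. Use pre-intervention information where it exists. The article documents none, so otherwise use the earliest records and the more stable features (management style, group type, frequency of multi-problem families).
3. Where feasible, have an existing team member code without knowledge of arm, and lock the coding before t2 outcomes are opened.
4. Report the second hypothesis as exploratory, given about 25% power for a 0.5 SD interaction under the 4/3 split.

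The cost is a short coding form, some coding time and revised wording, and more effort if early information has to be gathered. The downside is less rich moderator data. If only early-intervention records exist, the risk is reduced but not removed.
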